**Methods and analysis:**

Three academic centres in Québec will measure inflammatory biomarkers alongside BDR and/or BPT interpretation for patients with suspected asthma referred by primary care providers (PROPULSION SANTÉ, NCT06981169). Consenting patients aged ≥6 years will undergo FeNO, BEC and BDR testing. If BDR is non-diagnostic, subsequent BPT will be prioritised for patients with ≥1 elevated biomarker (BEC ≥300 /µL, (FeNO ≥25 ppb if ≥12 years or FeNO ≥20 ppb if <12 years)); others will follow usual timelines. Reports to the referring healthcare providers will include standard interpretation of BDR/BPT and biomarker results to state exacerbation risk and suggested corticosteroid dosage. Asthma control and quality of life will be assessed at baseline and remotely at 4, 8 and 12 months. The primary outcome will be the delay from the reception of test request for the diagnosis of asthma patients with versus without elevated biomarker(s). Secondary outcomes include biomarkers’ diagnostic performance, asthma control, quality of life, health benefits, cost-effectiveness, environmental impact and patient satisfaction. We aim to recruit 1500 patients to PROPULSION SANTÉ, with optional biobanking for translational sub-studies for 123 adults (DIVE, NCT05992519) and 123 children (DIVE2, NCT07011394).

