European guidelines recently incorporated FeNO as an effective alternative and cost-effective diagnostic tool for asthma and to optimise access to specialised testing : a FeNO level ≥40 ppb is 90% specific for asthma diagnosis in adults.^29 30^ The United Kingdom’s National Institute for Health and Care Excellence (NICE) guidelines recommend using FeNO and BEC early in the diagnostic algorithm as a first-line diagnostic tool before spirometry or peak flow monitoring.^29 30^ In children ≥5 years, only FeNO (≥35 ppb) has been validated as a first-line diagnostic test, while BEC had been used after BDR and PEF, along with skin prick tests or specific IgE measurement.^29 31^ The introduction of FeNO testing as a first-line diagnostic tool is estimated to enable approximately 29 000 additional asthma diagnoses annually, leading to earlier treatment initiation, improved disease control, reduced absenteeism and potential cost savings of £100–204 million per year.^32^

In Quebec, over 3000 diagnostic tests are still pending across Centre Hospitalier Universitaire de Sherbrooke (CHUS), CHU Sainte-Justine (CHUSJ) and the Montreal Children’s Hospital (MHC), including 1300 tests for children, with wait times exceeding 1 year. BPTs are scheduled chronologically, with priority only for internal referrals, that is, for specialists of the institution. The lack of robust prospective data on FeNO and eosinophils (and limited FeNO access) has restricted their integration into diagnostic algorithms.

Our overarching aim is to address an evidence gap by evaluating the integration of inflammatory biomarkers into referral for the asthma diagnosis specifically from primary or community care under real-world conditions. Specifically, we aim to assess whether FeNO and BEC can improve the prioritisation of patients for bronchial provocation testing (BPT), thereby streamlining referrals and supporting more timely and cost-effective asthma diagnosis. Propulsion Santé also includes two translational sub-studies: DIVE (in adults) and DIVE-2 (in children) involving additional sampling (serum and nasal epithelial lining fluid (NELF)) to link inflammatory mediators (alarmins, interleukins and eicosanoids), diagnosis and T2 biomarkers to gain mechanistic insight at the point of diagnosis in primary care.

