### Intervention

The interpretation of respiratory function tests and biomarkers will be performed by the principal investigator pulmonologist at each centre or by trained designated collaborating pulmonologists by following these models:

High-risk inflammatory asthma is defined by FeNO ≥25 ppb or BEC ≥300 cells/µL in participants ≥12 years (≥20 ppb or ≥300 cells/µL in children aged 6 to <12 years)^15 50^ : one or more elevated biomarkers will be interpreted as a high risk of asthma exacerbation. If spirometry is non-diagnostic, BPT will be prioritised (<2–4 weeks).Low risk inflammatory asthma is defined by FeNO <25 ppb and BEC <300 cells/µL (<20 ppb or <300 cells/µL in children aged 6–<12 years)^15 50^: this will be interpreted as a low risk of asthma exacerbation. If spirometry is non-diagnostic, BPT will be scheduled according to the standard waiting list.

Results of biomarkers will be integrated on the medical report indicating the probability (high/low) of asthma exacerbation and suggested management with either ICS taken as-needed (T2-low) or regularly (T2-High) ICS if clinically appropriate, which will be forwarded to the referring physician.

The patient test pathway based on their respiratory test and the results of the inflammometry assessment is summarised in figure 2.

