**Figure 2 F2:**
[figure not shown]
Flow Diagram. Patients with suspected asthma are referred by primary care for pulmonary function testing (BDR or BPT). Those who consent to participate in the study will undergo BEC and FeNO testing. Patients with normal spirometry results and at least one elevated inflammatory marker will have their methacholine challenge test prioritised. If no inflammatory markers are elevated, the BPT will be scheduled within standard timelines. Patients undergoing a BPT—either directly on referral or after an initial BDR—will be invited to participate in the translational research studies, DIVE for adults or DIVE2 for children. Patients with a confirmed diagnosis of asthma (based on spirometry or BPT) will also be stratified according to their inflammometry results, which will be included in the report sent to the referring physician. BEC, blood eosinophil count; BDR, bronchodilator reversibility; BPT, bronchial provocation testing; FeNO, fraction exhaled of nitric oxide.

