#### Secondary Outcomes

Diagnostic accuracy of inflammometry assessed through receiver operating characteristic (ROC) curve analyses using FeNO levels, BEC and their combined values, with BPT as gold standard. Clinically relevant thresholds will be identified to optimise rule-in capacity for asthma diagnosis in primary care, targeting ≥90% of specificity and a positive likelihood ratio (LR+) ≥10 in children, adolescents and adults (as three distinct subgroups).Assessment of inflammatory status on asthma control, evaluated pre-diagnosis and post-diagnosis using the ACQ-5, ACT and EQ-5D-5L questionnaire scores. Additional measures include the number of exacerbations, prescribed and dispensed medications and the frequency of specialised asthma consultations collected from clinical records, drug claims and patient electronic reports at baseline and at 4-month, 8-month and 12-month follow-up.Assessment of health benefits in terms of QALY, budget impact and economic efficiency (evaluated using incremental cost-effectiveness ratio (ICER) and Incremental cost-utility ratio (ICUR)) of integrating inflammatory biomarkers into primary care asthma diagnosis.The evaluation of annualised carbon dioxide (CO2) emissions from inhalers dispensed to non-asthmatic individuals awaiting their diagnostic tests was done based on drug claims and Cascades Canada environmental data.^27^ Environmental sustainability assessment of biomarker-enabled pathways will be explored.Descriptive analysis of patient satisfaction regarding inflammometry and the overall experience of diagnostic procedures, with responses stratified by age (6–<12, 12–<18, ≥18) and diagnostic test (BDR or BPT) and final asthma diagnosis status.

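### Report timing is unclear: biomarker-matched ICS advice could reach the referrer before the BPT, so treatment ahead of the reference test could depend on the index test

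*Protocol article*

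**What the plan says.** All references are to the protocol article.

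- **Report content.** The Abstract (Methods and analysis) says: "Reports to the referring healthcare providers will include standard interpretation of BDR/BPT and biomarker results to state exacerbation risk and suggested corticosteroid dosage". The Intervention section adds the biomarker-specific content: "suggested management with either ICS taken as-needed (T2-low) or regularly (T2-High) ICS if clinically appropriate, which will be forwarded to the referring physician". Neither passage limits the suggestion to patients with a final diagnosis, and neither says when the report is sent.
- **Figure 2 caption.** "Patients with a confirmed diagnosis of asthma (based on spirometry or BPT) will also be stratified according to their inflammometry results", and the caption places that stratification in the report to the referrer.
- **Time between the two tests.** For patients with a raised biomarker: "If spirometry is non-diagnostic, BPT will be prioritised (<2–4 weeks" (parenthesis closes there). For the others: "BPT will be scheduled according to the standard waiting list". The Introduction describes the pending tests at the three centres "with wait times exceeding 1 year".
- **Accuracy analysis.** Secondary Outcomes specifies ROC analyses of FeNO, BEC and their combination "with BPT as gold standard", with rule-in targets of at least 90% specificity and LR+ of at least 10. The CO2 outcome counts inhalers dispensed to people found not to have asthma while they waited for testing.
- **Corticosteroids before testing.** Table 1 lists washout periods for short- and long-acting β₂-agonists and muscarinic antagonists, and has no corticosteroid row. The Participants section excludes recent corticosteroid use (48 hours) for DIVE and DIVE2 only. Refusal is the sole exclusion from the main study.

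**The concern.** In an accuracy study, nothing that depends on the index test should change the reference test result. Here the biomarkers are the index test and the BPT is the reference. On one reading of the Intervention section, a patient with a non-diagnostic BDR and a raised biomarker has a regular-ICS suggestion sent to the referrer while the BPT is still to come. A patient without a raised biomarker has an as-needed suggestion sent and waits on the standard list.

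If treatment turned some biomarker-positive asthmatics BPT-negative, the analysis would count them as biomarker false positives. That lowers apparent specificity and LR+, the two quantities the rule-in cut-offs must satisfy, and pushes the selected cut-offs upward. The same patients would be labelled non-asthmatic, so their inhalers would enter the CO2 outcome as treatment of people without asthma.

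**Working it through.** **Step 1. The passages side by side.** The Abstract and the Intervention section attach the ICS suggestion to the report without requiring confirmed asthma. The Intervention section makes the attachment straight after describing what happens when spirometry is non-diagnostic. The Figure 2 caption describes inflammometry in the report for confirmed asthma, though it does not say only for those patients. Both early and late release are compatible with some part of the text, and no sentence settles which applies.

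**Step 2. Is the exposure handled elsewhere?** There is no corticosteroid washout row, and the 48-hour exclusion is confined to the sub-studies. The listed sensitivity analyses cover active smokers, each biomarker alone, paediatric-only sites and alternative diagnostic criteria. None concerns ICS started between tests. The Discussion names medication use as a source of biomarker variability, not of BPT misclassification. Respiratory medication is asked about at the visit, but reMed dispensing data cover public-plan members only.

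**Step 3. Illustration of size.** The plan gives no figure of its own to reproduce here. The inputs are assumptions:

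- Sensitivity Se = 0.5. This borrows the Introduction's statement that half of asthmatics have T2 inflammation, which is not the sensitivity of any FeNO or BEC cut-off.
- Specificity Sp = 0.9, the plan's target.
- Proportion with asthma p = 1/2 (assumed) or 2/3 (the 2:1 ratio in the DIVE sample size).
- q = share of biomarker-positive asthmatics who turn BPT-negative on ICS. The documents give no value.

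Formulas:

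- TP = p·Se; TN = (1−p)·Sp; FP = (1−p)(1−Sp); moved = q·TP
- Apparent specificity = TN / (TN + FP + moved)
- Apparent sensitivity = (TP − moved) / (TP − moved + p(1−Se))
- LR+ = apparent sensitivity / (1 − apparent specificity)

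For p = 1/2 and q = 0.05, moved = 0.05 × 0.25 = 0.0125. Specificity = 0.45 / 0.5125 = 0.878, and sensitivity = 0.2375 / 0.4875 = 0.487.

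| Asthma : non-asthma | q | Apparent specificity | LR+ | Asthmatics within the non-asthma group |
|---|---|---|---|---|
| any | 0 | 0.900 | 5.0 | 0% |
| 1:1 | 5% | 0.878 | 3.99 | 2.4% |
| 1:1 | 10% | 0.857 | 3.32 | 4.8% |
| 2:1 | 5% | 0.857 | 3.41 | 4.8% |
| 2:1 | 10% | 0.818 | 2.61 | 9.1% |

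With p = 0.40 and Se = 0.3, the effect is smaller: specificity is 0.891 at q = 5% and 0.882 at q = 10%. Across these settings, each 5% moved costs roughly 1 to 4 specificity points.

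**Step 4. Movement in the other direction.** Biomarker-negative asthmatics who turn BPT-negative add to the true negatives and raise apparent specificity. With Sp = 0.9, they cancel the fall only if they number nine times the biomarker-positive patients moved, since L/(L + H) = 0.9 requires L = 9H (L = biomarker-negative, H = biomarker-positive patients moved).

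**Step 5. Would restricting to untreated patients cure it?** Suppose 30% of biomarker-positive patients are dropped regardless of disease. Sensitivity becomes 0.35 / (0.35 + 0.50) = 0.41, specificity 0.90 / (0.90 + 0.07) = 0.93, and LR+ 5.7. The restricted set is distorted by about 3 points in the optimistic direction, comparable to the 2-point loss at 1:1 with q = 5%.

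**The case against.** The strongest reply is that bias needs four things to happen: the suggestion is released before the BPT, the referrer acts on it, the patient takes regular ICS, and the BPT turns negative within the short prioritised interval. The documents quantify none of the last three, and the Figure 2 caption points away from the first. **This stands.** The bias is possible, not shown.

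A reader might infer that the protocol assigns treatment by biomarker status. It does not: it describes a suggestion to the referrer, qualified by clinical appropriateness. Nor does the missing corticosteroid row show that ICS continues up to the methacholine test.

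Other parts of the reply also stand:

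- Patients sent directly to BPT, with biomarkers taken at that visit, have no interval in which the result could act. They dilute any effect.
- DIVE and DIVE2 have at least partial protection from their 48-hour exclusion.
- The illustration treats the triage thresholds as though they were the rule-in cut-offs, which the plan has still to identify. Its unbiased LR+ of 5.0 already misses the target of 10, so it does not show that bias would cause that failure.
- Supplemental table S2, which lists all collected variables, is not shown and may include medication dates. An ROC subset by ICS exposure could also be left to an analysis plan.

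The reply does not resolve the disagreement between sections over when the suggestion is reported. It also does not make exposure that went unrecorded at the BPT visit easy to recover later.

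**Conclusion.** The point holds as a conditional one. The text leaves open a biomarker-dependent treatment suggestion between index and reference test, and nothing described for the main study would detect or handle its effect. Specificity, LR+, the cut-offs and the non-asthmatic label can be biased. Neither the size nor, strictly, the net direction can be determined from the documents. In the illustration it would take nine biomarker-negative conversions for each biomarker-positive one to offset the fall.

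The fall from 90% to about 88–86% (1:1) or 86–82% (2:1) rests wholly on the assumed sensitivity, specificity and 5–10% conversion. It should not be read as a forecast.

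Severity is moderate. The outcomes touched are secondary: diagnostic accuracy and the descriptive CO2 outcome. The primary outcome runs from requisition to the date of the last confirmatory test, and a changed BPT result does not alter that date.

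**What to change.** 1. Reconcile the Abstract, the Intervention section and the Figure 2 caption on whether the ICS suggestion is reported before the confirmatory test or only after it. Which it should be is a clinical decision for the investigators.
2. At the BPT visit, record for every participant any ICS start, any change and the date of last use, unless table S2 already does so. reMed alone would miss people outside the public plan.
3. Keep all patients as the main ROC analysis. Pre-specify a sensitivity analysis that stratifies by, or excludes, corticosteroids started or stepped up between biomarker measurement and BPT. State that this subset is itself selected by biomarker result, so it should not replace the main analysis.
4. Report negative-BPT and CO2 results by ICS use at the BPT.

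The cost is a clarifying sentence, one medication item at a visit where respiratory medication is already asked about, and one extra analysis with lower precision in the subset.

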**Figure 2 F2:**
[figure not shown]
Flow Diagram. Patients with suspected asthma are referred by primary care for pulmonary function testing (BDR or BPT). Those who consent to participate in the study will undergo BEC and FeNO testing. Patients with normal spirometry results and at least one elevated inflammatory marker will have their methacholine challenge test prioritised. If no inflammatory markers are elevated, the BPT will be scheduled within standard timelines. Patients undergoing a BPT—either directly on referral or after an initial BDR—will be invited to participate in the translational research studies, DIVE for adults or DIVE2 for children. Patients with a confirmed diagnosis of asthma (based on spirometry or BPT) will also be stratified according to their inflammometry results, which will be included in the report sent to the referring physician. BEC, blood eosinophil count; BDR, bronchodilator reversibility; BPT, bronchial provocation testing; FeNO, fraction exhaled of nitric oxide.

### Data and sample management

Participant data will be collected prospectively in REDCap and stored on encrypted servers with restricted access hosted at the University of Sherbrooke.^33^ Follow-up will be conducted via REDCap emails with reminders after 15 days of no response.

BEC will be performed in each institution’s clinical laboratory (complete blood count with differential), after sampling in an EDTA tube. Blood samples will be processed within 4 hours of collection according to standardised protocols. For participants enrolled in the complementary DIVE or DIVE 2 studies, additional sample processing will include plasma separation, peripheral blood mononuclear cell separation and preservation of whole blood and DNA for future methylation analyses, following standardised biobanking protocols: inflammatory protein quantification will be performed on serum and NELF for IL-4, IL-5, IL-13, IL-33, thymus associated regulatory cytokine (TARC), thymic stromal lymphopoietin (TSLP), eotaxin-3, interferon gamma (IFNγ) and tumour necrosis factor (TNF) using multiplex electrochemiluminescent assays (MesoScale Discovery) and ELISA.

### Outcomes measures

#### Primary Outcome

The primary outcome, diagnostic delay, will be defined as the interval between primary care requisition for pulmonary function testing and the last confirmatory diagnostic test conducted (BDR or BPT). This continuous outcome will be analysed longitudinally and stratified by biomarker-guided diagnostic strategies, also adjusting for the time of inclusion in the study. Sensitivity analyses will also examine diagnostic delay for FeNO and blood eosinophils considered separately.

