### Participants

Eligible participants are individuals aged ≥6 years who present with symptoms suggestive of asthma and have been referred by primary care (family physicians and nurse practitioners) or community practice (eg, paediatricians and other non-pulmonologist physicians) for asthma diagnosis at one of the three participating centres. Participants are identified from an existing waiting list of approximately 3000 patients awaiting respiratory function testing. The only exclusion criterion for PROPULSION SANTÉ is refusal to participate in the study.

Among these patients, a target sample of 123 adult participants (aged≥18 years) and 123 paediatric participants (aged 6–18 years) undergoing BPT will be consecutively invited to participate in the DIVE and DIVE-2 sub-studies, respectively, regardless of their T2 status. DIVE/DIVE2 inclusion requires non-diagnostic spirometry and no contraindication to methacholine challenge. Patients will be excluded from participation if they meet any of the following conditions: use of inhaled or systemic corticosteroids within 48 hours prior to testing; tobacco use within the previous 6 hours; diagnosis of chronic obstructive pulmonary disease (COPD), defined as all of the following — age ≥40 years, fixed airway obstruction on spirometry (FEV1/Forced Vital Capacity (FVC)<0.7) and a smoking history >10 pack-years or documented alpha-1 antitrypsin deficiency— and evidence of parenchymal lung disease (such as cystic fibrosis or bronchiectasis), unstable cardiac disease or a history of acute respiratory infection (viral or bacterial) within the preceding 4 weeks.

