For the primary outcome of waiting time differences, the baseline diagnostic delay, prior to the project implementation, will be established based on the time elapsed between the initial request for an asthma diagnostic test made by primary care and the performance of that test. During the intervention, diagnostic delays will be monitored prospectively, both overall and stratified by inflammatory status. We will apply linear mixed-effects models with restricted maximum likelihood estimation. These models will incorporate (high-risk vs low-risk), study period at time of inclusion, and the number of awaiting tests as fixed effects. Random effects will account for within-centre clustering and repeated measurements. In addition, Kaplan-Meier survival curves will be constructed to visualise the probability of remaining undiagnosed over time for both high-risk and low-risk inflammatory phenotypes. These curves will allow for a graphical representation of differences in diagnostic efficiency between groups. Cox proportional hazards regression will be used to identify significant predictors of waiting time with HRs and 95% CIs reported.

Diagnostic performance in the secondary outcome will be evaluated through ROC analysis, calculating the area under the curve (AUC) with 95% CIs for each individual marker and for their combined use. Sensitivity, specificity, positive and negative predictive values and likelihood ratios will be calculated with their respective 95% CIs.

Health utility values will be derived from EQ-5D questionnaires^39 52 53^ completed at baseline and follow-up visits. Quality-adjusted life years will be calculated using the AUC method, connecting utility values across measurement time points. This approach integrates health-related quality of life over the 12-month follow-up period. To assess the financial implications of implementing FeNO testing within the provincial healthcare framework, we will develop a budget impact model for the MSSS. Environmental and satisfaction-related outcomes will be analysed using descriptive statistics. CO₂ emissions from inhalers dispensed to non-asthmatic individuals will be estimated based on Cascades Canada data,^27^ and patient satisfaction with inflammometry will be assessed using structured questionnaires.

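### The primary delay has no single end point: a patient with a non-diagnostic BDR and no BPT can be scored as finished at the BDR or left without an end date

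*Protocol article*

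**What the plan says.** The end of the primary delay is worded in four ways.

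- Primary Outcome: the delay is "the interval between primary care requisition for pulmonary function testing and the last confirmatory diagnostic test conducted (BDR or BPT".
- Abstract, Methods and analysis: the outcome is the "delay from the reception of test request for the diagnosis of asthma patients with versus without elevated biomarker(s".
- Statistical methods, for the baseline period before the project: "the time elapsed between the initial request for an asthma diagnostic test made by primary care and the performance of that test".
- Statistical methods, for the Kaplan-Meier curves: they are to "visualise the probability of remaining undiagnosed over time".

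On analysis, the Primary Outcome section adds: "This continuous outcome will be analysed longitudinally and stratified by biomarker-guided diagnostic strategies". Statistical methods then states: "We will apply linear mixed-effects models with restricted maximum likelihood estimation". Cox regression is also planned, but the article names no event or censoring rule for it or for the Kaplan-Meier curves.

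On who can be enrolled, Participants says "The only exclusion criterion for PROPULSION SANTÉ is refusal to participate in the study". The methacholine restriction applies only to the sub-studies: "DIVE/DIVE2 inclusion requires non-diagnostic spirometry and no contraindication to methacholine challenge". Study design expects every patient with a non-diagnostic BDR to go on to BPT, and the Introduction puts inconclusive spirometry at up to 80% of cases.

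**The concern.** The main study can enrol patients who will never have a BPT because methacholine is contraindicated, or because they decline or do not attend. For them the four wordings give different answers. A test-based reading ends the delay at the BDR although asthma has been neither confirmed nor excluded. A diagnosis-based reading gives no end date.

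The choice affects the primary contrast because the groups differ by design in the wait after the BDR. Patients with an elevated biomarker (T2-high) get a prioritised BPT, and the others (T2-low) join the standard list. Closing a patient at the BDR deletes a short wait in the first group and a long one in the second. Leaving the patient without an end date removes them from a linear model that has no censoring. Two analysts following the article could report different primary results.

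**Working it through.** **1. What each reading does to each patient**

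| Path | Any conducted test ends the delay | Only a positive test ends the delay | Kaplan-Meier label |
|---|---|---|---|
| Diagnostic BDR | ends at BDR | ends at BDR | diagnosed |
| Non-diagnostic BDR, positive BPT | ends at BPT | ends at BPT | diagnosed |
| Non-diagnostic BDR, negative BPT | ends at BPT | no end date | unclear |
| Non-diagnostic BDR, no BPT | ends at BDR | no end date | still undiagnosed |

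No column treats the last two rows satisfactorily. The first gives a complete delay to an unresolved patient. The second drops everyone in whom asthma was ruled out. The third does not say whether ruling out asthma ends the undiagnosed state.

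**2. Inputs for an illustration.** The article gives no figure for this point, so there is none to reproduce.

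- T2-high wait from BDR to BPT: 21 days, within the two to four weeks in Intervention.
- T2-low wait: 365 days (assumed). The Introduction reports waits of over a year for pending tests, but not for the BDR-to-BPT interval. 180 days is used as a lower value.
- Shares never having BPT, p_high and p_low: assumed.

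**3. Closing at the BDR, among BDR-non-diagnostic patients.** The requisition-to-BDR wait is taken as equal in the two groups and cancels.

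Difference if every BPT is done: 365 − 21 = 344 days.

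Scored difference = (1 − p_low) × 365 − (1 − p_high) × 21.

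- 5% high, 10% low: 328.5 − 19.95 = 309 days (−10%)
- 5% high, 20% low: 292 − 19.95 = 272 days (−21%)
- 10% high, 30% low: 255.5 − 18.9 = 237 days (−31%)

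Unequal shares are not needed. With 20% in both groups the result is 0.80 × 344 = 275 days (−20%).

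With a T2-low wait of 180 days the full difference is 159 days. The same three cases give 142, 124 and 107 days (−11%, −22%, −33%). The proportional loss depends mainly on the shares and little on the wait.

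**4. Closing at the BDR versus dropping the patient, over all patients.** Assume 80% non-diagnostic in both groups and everyone starting with a BDR. The full difference is 0.80 × 344 = 275 days. If never-tested patients are dropped and negative BPTs kept, each group's mean wait after the BDR is 0.80(1 − p)w / (1 − 0.80p), where w is that group's wait.

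| p_high, p_low | Closed at BDR | Dropped |
|---|---|---|
| 5%, 10% | 0.80 × 308.55 = 247 days | 285.7 − 16.6 = 269 days (−2%) |
| 5%, 20% | 0.80 × 272.05 = 218 days | 278.1 − 16.6 = 261 days (−5%) |
| 10%, 30% | 0.80 × 236.6 = 189 days | 268.9 − 16.4 = 253 days (−8%) |

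In the last row the two readings differ by about 63 days on the same data. Dropping negative BPTs as well cannot be sized, because the article gives no BPT-positive share by biomarker group.

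**The case against.** The strongest reply is that the definition contains the word *confirmatory*. A non-diagnostic BDR confirms nothing, and the mention of BDR is naturally explained by patients whose BDR is diagnostic. The abstract speaks of diagnosis, and the Kaplan-Meier label implies that an unresolved patient stays at risk. Kaplan-Meier and Cox methods can censor such patients. Event and censoring rules usually sit in a statistical analysis plan, which is not at hand.

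Much of this stands. A reader might infer that the plan prescribes closure at the BDR, so that undiagnosed patients are bound to count as short delays. The documents do not support that: the wording permits this scoring but does not require it. Nor is such a delay necessarily short, since the requisition-to-BDR wait still counts. A reader might also infer that T2-low patients will drop out more often. That is plausible after a long wait, but no figure in the article shows it.

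The reply does not rescue the definition. If *confirmatory* means positive, it also removes the end date of patients ruled out by a negative BPT. The baseline definition, which ends when the test is performed, points to the test-based reading. The stated model is linear, with no censoring. The point rests on wordings that are in print and disagree, so it goes beyond a detail left for later.

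**Conclusion.** The concern holds as an unresolved ambiguity in the primary end point, with a biased or selected contrast on either reading. On the test-based reading, never-tested patients get a falsely complete delay. In the illustration the contrast among BDR-non-diagnostic patients is then about 10–31% smaller. On the positive-test reading, these patients and those with a negative BPT drop out of the linear model, with an effect that cannot be sized from the article.

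The percentages rest on assumed never-tested shares and an assumed BDR-to-BPT wait. They show sensitivity and do not predict the result. Closure at the BDR biases towards the null, so it would not create a false benefit of prioritisation. It would understate the delay of the T2-low group and reward incomplete testing with a shorter delay.

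**What to change.** 1. End the delay at the first test that settles the diagnosis: a diagnostic BDR, or a completed BPT of either result. State that a non-diagnostic BDR never ends it. Bring the abstract and baseline wordings into line.
2. Use the same event for the Kaplan-Meier and Cox analyses. Censor patients with no BPT at last contact or data cut, and do not close them at the BDR. The same rule covers a BPT still pending at data cut.
3. Say that the linear mixed model then describes only patients whose diagnosis was settled.
4. Report the number without a BPT, and the reasons, by T2 group.
5. If long waits lead patients to give up, the censoring is informative. Add a sensitivity analysis that keeps these patients undiagnosed to the end of follow-up.

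The cost is one definition sentence, one censoring rule and one sensitivity analysis. Dates and reasons for BPT cancellation or non-attendance must be recorded; the article does not say that the waiting list holds them.
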